### Study group

All acute trauma patients are eligible for inclusion for the REACT trial when transported by the ambulance or helicopter to the AMC or VUmc shockroom according to the current pre-hospital triage system based on: Injury mechanism, Revised Trauma Score (RTS) and presence of traumatic brain injury. These factors determine the level of care that has to be present in the facility to which patients are transported.

The exclusion criteria for subsequent follow-up and analysis are patients younger than 16 years of age and patients who die during transport to the hospital.

The start of the study was scheduled for 1-11-2005.

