**Methods/design:**

The REACT-trial is a prospective, randomized trial, comparing two Dutch level-1 trauma centers, respectively the VUmc and AMC, with the only difference being the location of the CT scanner (respectively in the Radiology Department and in the shockroom). All trauma patients that are transported to the AMC or VUmc shockroom according to the current prehospital triage system are included. Patients younger than 16 years of age and patients who die during transport are excluded. Randomization will be performed prehospitally.

Study parameters are the number of days outside the hospital during the first year following the trauma (primary outcome), general health at 6 and 12 months post trauma, mortality and morbidity, and various time intervals during initial evaluation. In addition a cost-effectiveness analysis of this shockroom concept will be performed.

Regarding primary outcome it is estimated that the common standard deviation of days spent outside of the hospital during the first year following trauma is a total of 12 days. To detect an overall difference of 2 days within the first year between the two strategies, 562 patients per group are needed. (alpha 0.95 and beta 0.80).

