### Randomization

Randomization will be performed at the "Meldkamer Ambulancezorg Amsterdam" (MKA), the organization in charge of the coordination and distribution of ambulances and patients. Randomization will be performed using a computer program on a 1:1 basis with varying block sizes of 8, 12, and 16. Ambulance personnel will receive instructions according to the outcome of the randomization. Each eligible patient involved in a specific accident will be randomized. After each randomization, there is a pre-specified time interval of 1 hour in which eligible patients will be automatically transported to the other trauma center in order to minimize peak pressure in the study centers and guarantee optimal utilization of the two trauma centers. These patients are included in the trial, but are not formally randomized. In extreme cases, prehospital ambulance personnel can decide to waive the outcome of randomization, if they deem that the status of the patient requires the immediate attention of the closest hospital and death is imminent.

Because the distance between the two hospitals is relatively short (8 km) no significant delay in treatment by patient transport is encountered regardless of the outcome of the randomization.

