### Sample size

Based on the primary outcome criterion for both strategies, it is estimated that the common standard deviation is a total of 12 days. To detect an overall difference of 2 days in the number of days spent outside the hospital within the first year between the two strategies, 562 patients per group are needed for a two-sided significance level of 0.05 with a power of 0.80.

Based on historical data, we expect around 500 shockroom patients to be admitted on a yearly basis at each of the two participating centers. Therefore, the total number of eligible patients per year would be 1000 patients. We expect that a quarter of these patients will be excluded for various reasons (age < 16 yrs, lost to follow up, etc.) leading to a total of 750 inclusions per year. Consequently, a 1 1/2-year period should be sufficient to include the necessary total number of 1124 (2 × 562) patients.

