### Data analysis

The main analyses of primary and secondary outcomes will be conducted for all randomized patients according to the result of the randomization (intention-to-treat). Additional analyses include:

(1) Per-protocol analysis excluding patients that are transported to a different hospital rather than the result of the assignment procedure.

(2) Analysis of included patients treated either in the AMC or the VUmc independent of the randomization through the assignment procedure.

We will conduct both unadjusted and adjusted analyses. We will use gender, mechanism of trauma (sharp/blunt), initial Glasgow Coma Scale (GCS), RTS score and the presence of intubation to adjust for possible differences in severity of trauma between the AMC and VUmc patients.

For subgroup analysis the following analyses will be performed:

Hemodynamically unstable patients (non-responders (SBP < 90) vs. transient responders (SBP > 90 with continuous fluid requirement)); Sharp vs. blunt trauma patients; Patients prehospitally treated by Mobile Medical Teams; Neurotrauma patients; Presence or absence of a seatbelt sign; Torso trauma vs. isolated extremity trauma; Intubated vs. spontaneously breathing.

For final analysis standard statistical techniques will be used to compare the different outcomes between the two hospitals.

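### Patients who die during transport are excluded from analysis after prehospital randomization, which contradicts the stated intention-to-treat analysis of all randomized patients

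*Protocol article*

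**What the plan says.** Four statements in the protocol article bear on the point.

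- **Timing of allocation.** The abstract (Methods/design) says "Randomization will be performed prehospitally". The Randomization section adds that "Ambulance personnel will receive instructions according to the outcome of the randomization". The journey to hospital therefore follows the assignment.
- **Exclusions.** The Study group section says the "exclusion criteria for subsequent follow-up and analysis are patients younger than 16 years of age and patients who die during transport". The abstract repeats both exclusions.
- **Analysis set.** The Data analysis section says the main analyses of primary and secondary outcomes "will be conducted for all randomized patients according to the result of the randomization (intention-to-treat").
- **Endpoint.** The Endpoints section makes the primary outcome the number of days outside hospital in the first year. It describes this outcome as responsive to mortality, because a patient who has died accrues no further days.

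The Randomization section also states that, with the hospitals 8 km apart, patient transport causes no significant delay to treatment whatever the allocation.

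**The concern.** Age under 16 is fixed before allocation, so excluding on it does no harm if it is applied alike in both arms. Death during transport is different. It occurs after allocation, on a journey whose destination the allocation has set. Removing these patients from the analysis means the analysed set is no longer everyone randomized, which is what the Data analysis section claims.

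The patients removed also have the lowest possible score on the primary endpoint. If the number removed depended on the assigned hospital, the arm losing more of them would have its mean raised by the exclusion. The target difference is only 2 days on a scale of about 365, so few patients are needed for this to matter.

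**Working it through.** **1. The plan's own sample size.** Inputs from the Sample size section: SD 12 days, difference 2 days, two-sided 0.05, power 0.80, 562 per group.

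n per group = 2 × SD² × (1.960 + 0.842)² / difference² = 2 × 144 × 7.849 / 4 = 565.1, rounded up to 566.

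The stated 562 is within 0.7% of this and gives power 0.798. The stated size is reproduced; the problem is in the analysis set, not in this arithmetic.

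**2. The rules applied to one patient.** Take a patient of 16 or over who is randomized and dies on the way to the assigned hospital.

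| Rule | Outcome for this patient |
|---|---|
| Study group | Out of follow-up and analysis |
| Data analysis | Analysed in the assigned arm |
| Endpoints | Scores 0 days outside hospital |

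The first two rows cannot both be followed.

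**3. How many such patients equal the target effect.** Let m be the mean days outside hospital among the other patients. The article does not give m, so 330 to 360 is assumed. Suppose one arm has d more transport deaths than the other. With 562 other patients in that arm, excluding the d deaths rather than scoring them 0 raises its mean by d × m / (562 + d).

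| d | m = 330 | m = 350 | m = 360 |
|---|---|---|---|
| 1 | 0.59 days | 0.62 days | 0.64 days |
| 3 | 1.75 days | 1.86 days | 1.91 days |
| 4 | 2.33 days | 2.47 days | 2.54 days |
| 5 | 2.91 days | 3.09 days | 3.18 days |

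The imbalance that matches 2 days is about 2/m of an arm:

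- m = 330: 2/330 = 0.61%, and 0.0061 × 562 = 3.4 patients.
- m = 360: 2/360 = 0.56%, and 0.0056 × 562 = 3.1 patients.

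Equal numbers of deaths in the two arms would leave the difference almost unchanged.

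**4. What including them does to the spread.** If a share p of an arm scores 0, the variance is (1 − p) × 144 + p × (1 − p) × m². For one death in 562 (p = 1/562):

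- m = 330: 143.7 + 193.4 = 337, SD 18.4; n = 2 × 337.2 × 7.849 / 4, about 1,324 per group.
- m = 360: 143.7 + 230.2 = 374, SD 19.3; n = 2 × 373.9 × 7.849 / 4, about 1,468 per group.

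A single 0-day score per arm thus more than doubles the planned variance of 144.

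**The case against.** The strongest reply is that the exclusion is prespecified and openly stated, and that a death in the ambulance precedes either imaging strategy, so the location of the scanner cannot have caused it. The only route to bias is a difference in transport. The article says the 8 km distance causes no significant delay. In addition, "prehospital ambulance personnel can decide to waive the outcome of randomization" in extreme cases where death is imminent, so the patients most at risk can go to the closest hospital. An imbalance of three deaths that arises by chance is noise, not bias.

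Most of this stands, and it lowers the likely size of any bias. It does not reconcile the two sections. The waiver also concedes that the destination may matter for the patients most likely to die on the way.

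Three stronger readings are tempting, and the article does not support them.

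- **That diverted patients are dropped.** Eligibility applies "when transported by the ambulance or helicopter to the AMC or VUmc shockroom", which might suggest that patients taken elsewhere fall out. But that sentence refers to prehospital triage on factors that can be known before transport, and the Randomization section randomizes patients who are already eligible. The per-protocol analysis removes patients taken to a hospital other than the assigned one, which makes sense only if the intention-to-treat set keeps them.
- **That loss to follow-up is an analysis exclusion.** The Sample size section expects that "a quarter of these patients will be excluded for various reasons (age < 16 yrs, lost to follow up, etc".) This is an accrual allowance. The Study group section does not list loss to follow-up as an exclusion, and handling of missing outcomes may be in an analysis plan that is not shown.
- **That the arm with the longer journey will look healthier.** Nothing in the article says that either hospital is systematically farther from the patients.

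**Conclusion.** The contradiction is certain: the Study group section removes transport deaths after randomization, and the Data analysis section says everyone randomized is analysed. The harm is conditional. Only an imbalance caused by the assignment would bias the comparison, and the article gives no transport-death rates, overall or by arm. If other patients average 330 to 360 days, which is assumed, an excess of 3 to 4 excluded deaths in an arm of 562 (about 0.6%) equals the 2-day target. A reader should not take this as evidence that the trial is biased. The margin is too small, however, to leave the rule unresolved. The point rests on transport deaths alone.

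**What to change.** Define the intention-to-treat set as every randomized patient aged 16 or over. Keep patients who die during transport in their assigned arm, scored as 0 days outside hospital. Report the number of transport deaths by arm. Give the analysis without them as a sensitivity analysis, and amend the Study group section and the abstract to match.

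If the exclusion is to stay in the main analysis, the minimum is to call that set modified intention-to-treat, report the excluded deaths by arm, and add an analysis that restores them.

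The cost has two parts. Identity, assignment and date of death must be recorded for a few more patients. The outcome variance also grows: even one 0-day score per 562 takes the SD from the assumed 12 to about 18 or 19 (assuming a mean of 330 to 360 days for the others), and power for a 2-day difference falls accordingly. Deaths soon after arrival, which the plan already keeps, widen the spread in the same way, so excluding transport deaths would not by itself secure the SD of 12.

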### Randomization

Randomization will be performed at the "Meldkamer Ambulancezorg Amsterdam" (MKA), the organization in charge of the coordination and distribution of ambulances and patients. Randomization will be performed using a computer program on a 1:1 basis with varying block sizes of 8, 12, and 16. Ambulance personnel will receive instructions according to the outcome of the randomization. Each eligible patient involved in a specific accident will be randomized. After each randomization, there is a pre-specified time interval of 1 hour in which eligible patients will be automatically transported to the other trauma center in order to minimize peak pressure in the study centers and guarantee optimal utilization of the two trauma centers. These patients are included in the trial, but are not formally randomized. In extreme cases, prehospital ambulance personnel can decide to waive the outcome of randomization, if they deem that the status of the patient requires the immediate attention of the closest hospital and death is imminent.

Because the distance between the two hospitals is relatively short (8 km) no significant delay in treatment by patient transport is encountered regardless of the outcome of the randomization.

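### The sample size counts all included patients, but the main analysis takes only randomized ones; patients routed under the 1-hour rule are the uncounted difference

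*Protocol article*

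**What the plan says.** Three sections of the protocol article bear on this.

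- **Randomization.** Allocation is 1:1 by computer at the ambulance dispatch organization. The section states that "Each eligible patient involved in a specific accident will be randomized". It then sets a one-hour interval after each randomization, during which eligible patients go automatically to the other trauma centre. Of these it says: "These patients are included in the trial, but are not formally randomized".
- **Sample size.** The calculation assumes an SD of 12 days and a difference of 2 days, and concludes that "562 patients per group are needed for a two-sided significance level of 0.05 with a power of 0.80". For feasibility it takes 1000 eligible patients per year, removes a quarter (age under 16, loss to follow-up and similar), and arrives at 750 inclusions per year. From this it infers that "a 1 1/2-year period should be sufficient to include the necessary total number of 1124 (2 × 562) patients".
- **Data analysis.** The main analyses "will be conducted for all randomized patients according to the result of the randomization (intention-to-treat"). A second additional analysis takes included patients by the hospital that treated them, regardless of randomization.

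**The concern.** Recruitment is counted in one unit and the primary analysis in another. Patients routed under the 1-hour rule count toward 1124 because they are included, but drop out of the main analysis because they are not randomized. They cannot be absorbed in the quarter already deducted: that quarter is excluded, whereas the Randomization section calls these patients included. The sample-size section makes no other allowance for them.

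Two things are at stake. The first is power: if recruitment follows the sample-size section, the randomized set is smaller than the one the calculation calls for. The second is the definition of the main set. Whether a second or third victim of the same accident is randomized or routed automatically decides whether that patient belongs to it, and the Randomization section can be read either way.

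**Working it through.** **Inputs from the protocol (Sample size and Randomization sections):** two-sided alpha 0.05, power 0.80, SD 12, difference 2, allocation 1:1, 1000 eligible and 750 included per year, 1.5 years of accrual, one-hour window after each randomization.

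**Step 1. Reproduce 562.** n per group = 2 × [SD × (z₀.₉₇₅ + z₀.₈₀) / difference]².
- With unrounded normal quantiles this is 565.1, so 566.
- With (z₀.₉₇₅ + z₀.₈₀)² rounded to 7.8 it is 2 × 144 × 7.8 / 4 = 561.6, so 562.
- Power at 562 per group is 79.8%.

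The stated figure stands on its own inputs.

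**Step 2. Planned accrual.** 750 × 1.5 = 1125 inclusions, against 2 × 562 = 1124. Taken at face value there is no slack: two automatically routed patients leave 1123 randomized.

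**Step 3. Share routed automatically (an assumption; the documents give none).** Suppose arrivals are evenly spread (Poisson) at r per hour and only a randomization opens a window. Each randomization is then followed on average by r automatic patients, so the non-randomized share is f = r / (1 + r).
- 750 per year: r = 750 / 8760 = 0.0856, f = 7.9%
- 1000 per year: r = 1000 / 8760 = 0.1142, f = 10.2%

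The two rates bracket the relevant flow. Some of the excluded quarter, such as patients later lost to follow-up, would still have triggered a randomization and opened a window.

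**Step 4. Randomized number and power.** Randomized total = 1125 × (1 − f). Power = Φ{2 / [12 × √(2/n)] − 1.96}, with n per group.

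| f | Randomized | Per group | Power | Inclusions for 1124 randomized | Months at 750/year |
|---|---|---|---|---|---|
| 2% | 1102 | 551 | 79.0% | 1147 | 18.4 |
| 5% | 1069 | 534 | 77.8% | 1184 | 18.9 |
| 7.9% (750/year) | 1036 | 518 | 76.5% | 1221 | 19.5 |
| 10.2% (1000/year) | 1010 | 505 | 75.4% | 1253 | 20.0 |
| 20% | 900 | 450 | 70.5% | 1405 | 22.5 |

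At the protocol's own rates, 1125 − 1036 = 89 to 1125 − 1010 = 115 of the inclusions would not be randomized. The 2%, 5% and 20% rows only show sensitivity. Arrivals bunched at peak hours would raise f, because more patients would then fall within an hour of another.

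**The case against.** Several points on the other side have weight.

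- **The shortfall is conditional.** The 1.5 years is a forecast, not a stopping rule, and it rests on round figures (about 500 patients per centre, a quarter lost). The margin of one patient should not be taken literally. About 20 months of accrual would restore 562 randomized per group under the assumption above. This stands: the mismatch is in the text, but failure to reach 562 follows only if accrual ends at 1.5 years or at 1124 inclusions.
- **The main set is already restricted to randomized patients.** A reader might infer that the primary comparison is contaminated by patients whose destination was known beforehand. The Data analysis section does not support that. It confines the main analysis to randomized patients, and the automatically routed ones enter only the additional analysis by treating hospital. Predictable allocation would matter only if the written plan were departed from. This objection stands, but it leaves the count unrepaired.
- **The two sentences on accidents may be compatible.** They can be read as individual randomization of everyone in one accident, with the 1-hour rule for later, unrelated patients. A flat contradiction is therefore not shown. The text does not state that exception, however, so the ambiguity remains.
- **It could be left to an analysis plan.** That holds for details such as variance estimation for the additional analysis. It does not hold for the counting unit, because the protocol itself fixes both the target and the main set.

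**Conclusion.** The concern holds as a mismatch of counting units: 1124 is set against inclusions, while the main analysis uses randomized patients. With evenly spread arrivals at 750 to 1000 per year and accrual ending at 1.5 years or 1124 inclusions, the main set has about 1010 to 1036 patients (505 to 518 per group). Power is about 75 to 77% rather than 80%, a loss of roughly 3 to 5 points on the plan's SD of 12 and difference of 2.

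The mismatch itself needs no outside figure; its size does. A reader might infer a much larger loss, for example a quarter of patients not randomized, which would put power near 68% (1125 × 0.75 = 844 randomized). That would need day/night peaks and a rate of multi-victim accidents that the documents do not give. It would also need the 1-hour rule to override the sentence that each eligible patient in an accident is randomized. It should not be presented as the expected result.

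This should be fixed, but it does not threaten the validity of the stated main analysis.

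**What to change.** 1. Count 2 × 562 on formally randomized patients. Under the assumption above this needs about 1221 to 1253 inclusions, or 19.5 to 20.0 months at 750 per year. Alternatively, keep 1.5 years and state the expected randomized number (about 1010 to 1036), the resulting power (about 75 to 77%) and the assumed share routed under the 1-hour rule.
2. Say explicitly that automatically routed patients stay out of the main analysis, as the Data analysis section already implies. Report them by assigned centre only in a labelled additional analysis. The existing second additional analysis groups by treating hospital and does not do this.
3. Reconcile the two sentences in the Randomization section, so that it is clear whether further victims of one accident are randomized or come under the 1-hour rule.

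The cost is a few sentences, plus either one and a half to two more months of accrual or a slightly less favourable stated power. The counting and analysis-set changes need no change to ambulance routing.

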### Sample size

Based on the primary outcome criterion for both strategies, it is estimated that the common standard deviation is a total of 12 days. To detect an overall difference of 2 days in the number of days spent outside the hospital within the first year between the two strategies, 562 patients per group are needed for a two-sided significance level of 0.05 with a power of 0.80.

Based on historical data, we expect around 500 shockroom patients to be admitted on a yearly basis at each of the two participating centers. Therefore, the total number of eligible patients per year would be 1000 patients. We expect that a quarter of these patients will be excluded for various reasons (age < 16 yrs, lost to follow up, etc.) leading to a total of 750 inclusions per year. Consequently, a 1 1/2-year period should be sufficient to include the necessary total number of 1124 (2 × 562) patients.

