### Endpoints

The primary outcome criterion used is the number of days spent outside the hospital in the first year following the trauma. This outcome is responsive to differences in mortality (no additional days outside hospital), to differences in hospital stay for the initial admission and to differences in readmission rate.

The secondary outcome parameters include general health outcome at 6 and 12 months after the shockroom admission (using the EuroQol and HUI-3 questionnaires), morbidity and mortality during the first year following the trauma and various time intervals and process of care parameters of the initial admission (time to intervention, time to active bleed management, ICU and total hospital stay, etc.). Furthermore the radiation dosage is calculated in both strategies based on the actual number and type of radiological examinations related to the initial trauma performed in each patient during the first year.

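### The planning SD of 12 days does not fit a primary outcome in which deaths stop accruing days, so 562 per group does not give 80% power for a 2-day mean difference

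*Protocol article*

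**What the plan says.** The Endpoints section defines the primary outcome as "the number of days spent outside the hospital in the first year following the trauma". It gives mortality as the first reason for the choice: "This outcome is responsive to differences in mortality (no additional days outside hospital", followed by initial stay and readmission.

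The Study group section excludes only patients under 16 and "patients who die during transport to the hospital". Deaths after arrival therefore stay in, and the Data analysis section analyses all randomized patients as randomized. The Randomization section provides for a patient whose status "requires the immediate attention of the closest hospital and death is imminent", and Endpoints lists first-year mortality as a secondary outcome. No expected mortality is stated anywhere.

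The Sample size section, speaking of the primary outcome criterion in both strategies, says that "it is estimated that the common standard deviation is a total of 12 days". It then plans "To detect an overall difference of 2 days in the number of days spent outside the hospital within the first year" and concludes that "562 patients per group are needed for a two-sided significance level of 0.05 with a power of 0.80". The Abstract repeats the 12 days, the 2 days and the 562. No source is given for the 12 days.

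**The concern.** The outcome runs from 0 to 365 days. A patient who dies soon after arrival scores near 0, and most survivors score in the mid-300s. A few early deaths in a sample of this size add a variance component far larger than 12 squared. The planning SD therefore contradicts the definition of the outcome it is meant to describe.

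What is at stake is how the result is read. A null comparison of means would be taken to come from a trial with 80% power to find 2 days. If the real SD is several times larger, that reading is wrong. On a 350-day gap, a 2-day difference equals a mortality difference of 2/350 = 0.57 percentage points, so a small chance imbalance in deaths is enough to create or hide it.

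**Working it through.** **1. The plan's own figure.** Inputs from Sample size: difference 2, SD 12, two-sided alpha 0.05, power 0.80. Allocation is "on a 1:1 basis with varying block sizes of 8, 12, and 16" (Randomization).

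n per group = 2 × (1.960 + 0.842)² × 12² / 2² = 2 × 7.849 × 36 = 565.1.

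Rounding 7.849 to 7.8 gives 561.6, close to the stated 562. Power at 562 is 79.8%. The stated figure is thus a comparison of two means, correctly computed from SD 12.

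**2. How many early deaths SD 12 allows.** Assumptions: survivors average m = 350 days, early deaths score 0, and a share p of patients die early. With no variation among survivors,

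SD² = p(1 − p) × 350².

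Setting this to 144 gives p(1 − p) = 144/122,500 = 0.001176, so p = 0.118%. Among 1124 patients that is 1.3 deaths. With m = 335, p = 0.128%, or 1.4 deaths.

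**3. SD, power and detectable difference at 562 per group.** Now let survivors have the protocol's SD of 12:

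SD² = p(1 − p) × 350² + (1 − p) × 144

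SE = SD × √(2/562)

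Power for 2 days = Φ(2/SE − 1.96) + Φ(−2/SE − 1.96)

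Difference detectable with 80% power = 2.802 × SE

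Example, p = 5%: SD² = 5818.8 + 136.8 = 5955.6, so SD = 77.2 and SE = 4.60. Power is 7% and the detectable difference is 12.9 days.

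| Early mortality (assumed) | SD | Power for 2 days | Detectable with 80% power |
|---|---|---|---|
| 0 (as planned) | 12 | 80% | 2.0 days |
| 1% | 37 | 15% | 6.2 days |
| 2% | 50 | 10% | 8.4 days |
| 5% | 77 | 7% | 12.9 days |
| 10% | 106 | 6% | 17.7 days |

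With m = 335 the results hardly move: power is 16% at 1% mortality and 7% at 5%.

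**4. Deaths spread over the year.** As a lenient case, let deaths fall evenly over the year, so that their scores are uniform from 0 to 350. Then

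SD² = 350² × (p/3 − p²/4) + (1 − p) × 144.

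- Without survivor variation, SD 12 allows p = 0.35%, about 4 of 1124.
- With survivor SD 12, the SD is 23.4 at 1%, 45.8 at 5% and 62.5 at 10%.
- Power for 2 days is then 30%, 11% and 8%.

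The size of the loss depends on when deaths occur. The conclusion does not.

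**The case against.** **The magnitudes rest on assumptions.** The protocol gives no mortality rate and no mean for survivors, and deaths late in the year add less variance. This stands, so no single row of the table should be quoted as the trial's true power. It does not rescue the SD of 12, which fails once more than about 1 or 2 early deaths occur, or about 4 spread over the year.

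**The test is not fixed here.** The Data analysis section speaks only of standard techniques, and an analysis plan that is not shown may name the test. That is fair, and the absence of a named test is no part of this point. The stated calculation is nevertheless for a difference in means, and that statement is what fails.

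**A rank-based primary test might seem the natural cure.** The figures do not support that as a general remedy.

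- In simulations with 562 per arm and 5% deaths, Wilcoxon power was about 0.93 to 0.98 when survivors' stays were skewed and the benefit reached every stay.
- It was about 0.69 for a normal 2-day shift.
- It was about 0.09 when only the longest-staying fifth benefited.
- For a pure mortality effect (10% versus 5%, survivors' stay identical), Wilcoxon power was about 0.3 against about 0.9 for the t-test. For 5% versus 2% it was about 0.15 against 0.80.

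Making it primary would largely remove the responsiveness to mortality that the Endpoints section gives as a reason for the outcome.

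**Stronger readings that a reader might infer.** One is that the 562 is an arithmetic error; it is not, because only the SD input is at fault. Another is that a null result would be uninformative; that goes too far, because the same simulations show that a comparison of means keeps useful power for large mortality differences. A third is that the 12 days must be the SD of hospital stay in survivors; that is conjecture, since no source is given.

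**Conclusion.** The concern holds as a contradiction between the planning SD and the definition of the outcome. Given survivors near 350 days and early deaths near 0, the stated 80% power for a 2-day mean difference is not delivered unless almost nobody dies early. Over an assumed early mortality of 1% to 10%, power for 2 days is about 15% down to 6%, and the detectable difference is about 3 to 9 times the planned one (6.2/2 to 17.7/2). A null result on the mean should not be read as coming from a trial with 80% power for 2 days. This should be corrected before the results are interpreted.

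**What to change.** Keep the endpoint and the 1124 patients.

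1. Re-derive the SD from historical data, or from pooled blinded trial data, with deaths included and scored as the Endpoints section describes.
2. Restate the SD, the power for 2 days and the difference detectable with 80% power in the Abstract and in Sample size, and name the source of the SD.
3. Report one-year mortality and survivors' hospital days beside the primary result, so that a reader can see which component drives it.
4. If wanted, add a rank-based comparison as a sensitivity analysis, not as a replacement for the primary comparison.

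The cost is one rerun calculation and changes of wording, with no extra patients or data items. The downside is that the stated power for 2 days will look much less favourable.
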